# Telenursing Health Education and Lifestyle Modification Among Patients With Diabetes in Bangladesh: Protocol for a Pilot Study With a Quasi-experimental Pre- and Postintervention Design

**DOI:** 10.2196/71849

**Published:** 2025-05-09

**Keywords:** telenursing, health education, lifestyle modification, diabetic patients, Bangladesh

## Abstract

**Background:**

The global burden of chronic diseases is increasing and becoming a public health issue throughout the world. The use of telenursing is increasing significantly during and after the COVID-19 pandemic to treat and prevent chronic diseases. Telenursing is growing in many countries to reduce health care costs, increase the number of aging and chronically ill populations, and increase health care coverage to distant, rural, small, or sporadically populated regions. Among its many benefits, telenursing may help to solve increasing shortages of nurses, reduce distances, save travel time, and keep patients out of the hospital.

**Objective:**

The objective of this study is to apply the self-management telenursing program and telenursing system developed by the researchers to Bangladesh and to evaluate its feasibility and efficacy (improved diabetes control in participants).

**Methods:**

This is a pilot, quasi-experimental pre- and post-intervention study. Diabetes patients who will attend the Grameen Primary Health Centers (PHCs) in Bangladesh will be enrolled between September 2024 and August 2025. We include patients who have been diagnosed with type 2 diabetes, both sexes, ages 18-75 years old, all types of treatment, willing to participate and give us consent. We exclude patients who have been diagnosed with gestational diabetes, diabetes as a secondary cause, complication of chronic kidney disease (CKD) stage 5, Hemoglobin A1c (HbA_1c_) is less than 7% for the past 1 year with CKD stage 1 or 2, no complications or complications with good control, having enough knowledge (had education before) and implemented good practice regarding diabetes management assessed by the research nurses, and disabled persons who need other person’s support for daily living. The sample size was calculated and found 70. Written informed consent will be obtained from all the participants. The study protocol got approval from the National Research Ethics Committee of the Bangladesh Medical Research Council (BMRC/NREC/2022-2025/336) on September 08, 2024. The outcome of this study is to evaluate the effects of telenursing intervention by controlling HbA_1c_.

**Results:**

The project was funded in 2024. The enrollment of the participants started on October 26, 2024, and the required sample (n=70) enrollment was completed in February 2025. Data analysis will be started after completion of data collection and results will be expected to be submitted for publication in 2026.

**Conclusions:**

Diabetic patients will acquire disease-specific management skills. Setting and monitoring goals ensures the continuation of the desired behavior and gives the patients control over their lifestyle. After developing self-management skills, patients assess their lab data and lifestyles including diet, and understand their condition so that they can work with their physiological data by acquiring knowledge of both the disease and self-care. By making self-supported decisions, the patients will be able to manage their diet, exercise, and medication.

**Trial Registration:**

ClinicalTrials.gov NCT06632652; https://clinicaltrials.gov/study/NCT06632652

**International Registered Report Identifier (IRRID):**

DERR1-10.2196/71849

## Introduction

### Background

The global burden of noncommunicable diseases (NCDs) is increasing and becoming a public health issue throughout the world [1]. Globally, diabetes caused 1.6 million deaths and 47% of all deaths before the age of 70 years in 2021. Diabetes increases the risk of death from kidney and cardiovascular diseases [2]. The prevalence of diabetes has been increasing over the last few decades in all countries and is considered a global epidemic [3], more quickly in low- and middle-income (LMICs) countries than in high-income countries. Moreover, diabetic treatment coverage was the lowest in the low- and middle-income range in 2022 [4]. It is alarming that an estimated half of the global people (49.7%) living with diabetes remain undiagnosed [5]. Diabetes has acute complications including ketoacidosis, hypoglycemia, or hyperglycemia. Chronic complications are macroangiopathy, retinopathy, nephropathy, neuropathy, and diabetic foot. Patients with diabetes are vulnerable to infections, myopathy, osteoporosis, arthropathies, and liver damage [6]. Patients with diabetes may be able to prevent or delay diabetic health problems by maintaining a healthy lifestyle, taking medicine regularly, and controlling blood glucose levels [7].

The use of telenursing is increasing significantly during and after the COVID-19 pandemic to treat and prevent chronic diseases [8]. As a field, it is part of telemedicine and has many points of contact with other medical and nonmedical applications, such as telediagnosis, teleconsultation, and telemonitoring. The field, however, is still being developed as the information on telenursing is not comprehensive enough [9].

Telenursing has been adopted by many developed and developing countries. It reduces health care costs and increases the coverage of health care to outreach, rural, small, or sporadically populated regions [10]. It is useful for the increasing number of aging and chronically ill populations [11]. Among its many benefits, telenursing may help solve increasing shortages of nurses [12]; to reduce distances and save travel time and keep patients out of hospital [10]. A greater degree of job satisfaction has been registered among telenurses [13]. Continuous glucose monitoring (CGM) in patients with diabetes by integrating diagnostic devices for 24-hour real-time data transmission [14] and IBM Watson Health for personalized lifestyle optimization can help to identify and prevent the early appearance of diseases. It allows rural patients to receive personalized, high-quality care and improves health care access and outcomes [15].

### Diabetes in Bangladesh

The prevalence of diabetes was 9.2% (male: 8.8%, female: 9.6%) and prediabetes was 13.3% (male: 13%, female: 13.6%) in 2017. Among the patients, only 30.4% had controlled diabetes, 35.2% took treatment regularly and 61.5% were not aware of their diabetic condition. The factors related to getting diabetes were increasing age, overweight, and hypertension. The proportional mortality was 3% from diabetes of total death in all ages. In Bangladesh, 17% population was overweight (male: 14.4%, female: 19.6%), 3.3% were obese (male: 2%, female: 4.6%), and 25.1% had physical inactivity (male: 9.2%, female: 41.3%), those are the related risk factors for diabetes [16]. For the national response to diabetes, Bangladesh has an operational policy, strategy, and action plan for controlling diabetes and reducing physical inactivity, but not for reducing overweight and obesity. There are evidence-based national diabetes guidelines available, but not fully implemented. There are no set standard criteria for referral of patients from primary care to higher levels of care. In the primary care facilities, there are only blood glucose measurements and urine strips for glucose and ketone measurements generally available, but no facilities for insulin, metformin, sulphonylurea, oral glucose tolerance test, hemoglobin A_1c_ (HbA_1c_) test, dilated fundus examination, retinal photocoagulation, foot vibration perception by tuning fork, renal replacement therapy by dialysis, foot vascular status by Doppler, renal replacement therapy by transplantation in 2016 [17].

As there are no standard criteria for referring patients from primary care to a higher level of care, we will facilitate the patients to acquire self-management skills to understand the risk factors for diabetic complications and seek treatment in referral hospitals as necessary. They can attend referral hospitals to prevent diabetic complications by doing HbA_1c_ tests, dilated fundus examinations, retinal photocoagulation, foot vibration perception by tuning fork, renal replacement therapy by dialysis and transplantation, and also foot vascular status by Doppler.

### Study Objectives

#### General Objective

To apply the self-management telenursing program and telenursing system developed by the researchers to Bangladesh to evaluate its feasibility and efficacy (improved diabetes control in participants)

#### Specific Objectives

To control patients’ diabetic condition by measuring HbA_1c_.By having them acquire self-management behaviors and increase their self-efficacy, to minimize the risk of arising diabetic complications.To see the feasibility and barriers to implementing telenursing among patients with diabetes in Bangladesh.

#### Research Questions

Whether implementing a health education program will improve diabetic patient outcomes or not and will be operational and acceptable by the patients and health care professionals in Bangladesh.

#### Hypothesis

The diabetes self-management program developed by the researchers cannot improve the participants’ management of their diabetes (avoid aggravation, develop complications, and hospitalization) (H_0_) or can improve the participants’ management of their diabetes (H_1_).Is the telenursing system developed by the researchers operational in Bangladesh? Can the system be used by health care personnel (nurses) and patients? What are the obstacles and challenges, if any, in using the system?Is the diabetes self-management program developed by researchers acceptable to health care providers and patients? How about engagement? Will the program be continued (will there be dropouts)? If so, what are the reasons?

## Methods

### Design and Period

A pilot study with a quasi-experimental pre- and postintervention design will be implemented. As we will try to explore the participants’ characteristics, we want to conduct a pilot study to see the feasibility of this project among these participants. We plan to conduct quasi-experimental pre- and postintervention design, as we found in this setting randomization; case-control is rather difficult. Therefore, we will enroll the participants and collect baseline data and then we will educate them, and after 6 months we will evaluate them and compare the baseline (pretest) and the endline (posttest) data of individual participants. We set 6 months, as a previous study showed that a patient’s behavioral modification requires at least 6 months of intervention [18]. The study duration will be 1 year after getting approval from the Ethical Committee.

### Study Participants

The participants are people with diabetes, who take services from Grameen primary health centers (PHCs). We use 2 PHCs from Sahorail and Jamshahat of Manikganj District in Bangladesh.

#### Inclusion Criteria

The inclusion criteria are as follows:

Having been diagnosed with type 2 diabetesBeing of either sexBeing 18-75 yearsHaving a smartphone or mobile phoneWillingness to participate and give us consent

#### Exclusion Criteria

The exclusion criteria are as follows:

Patients who have been diagnosed as type 1 and gestational diabetesPatients whose diabetes are secondary causesPatients who have complications of chronic kidney disease (CKD) stage 5Patients whose HbA_1c_ has been less than 7% for the past 1 year with CKD stage 1 or 2, with no complications or complications with good control, have enough knowledge (had education before) and implemented good practice regarding diabetes management assessed by the research nurses (hereafter “the nurses”)Disabled persons who need other people’s support for daily living

### Sampling Technique

We will use a purposive sampling technique to select the participants. Patients who meet the eligibility criteria will be introduced by physicians at the PHCs, and the nurses will contact them at the PHC and obtain their consent.

### Sample Size

We calculated the sample size using G*Power software (version 3.1.9.7; Heinrich-Heine-University). As this is a pilot study, we set an effect size of 0.39 considering the differences between 2 dependent matched pair means of HbA_1c_ from a previous study [19], with a level of significance of 5%, and 80% power, the total sample size is calculated at 54. As patients have many options to discontinue the study (consent, withdraw, migration, change the health care facilities based on the disease severity, complications, hospitalization, etc), we consider a 30% dropout (16 participants) for this study. Therefore, the total sample size is estimated to be 70 (Textbox 1).

Output of software after generating sample size calculation.Effect size dz = 0.39α err prob = 0.05Input: Tail(s) = 2Power (1-β err prob) = 0.80Output: Noncentrality parameter δ = 2.8659030Critical *t*= 2.0057460Df = 53Total sample size = 54Actual power = 0.8033525

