**Figure 3 figure3:**
[figure not shown]
The 6-month program process.

In the third month, patients are requested to visit the PHC for regular follow-up by physician and laboratory test. In the sixth month group evaluation for 1 hour and endline data will be collected by the nurses at the PHC.

Patients will start implementing diabetes management right after group education. Each patient will develop monthly goal settings (behavior change plan) related to their diabetes management, daily practice them, and record the results every day in the self-monitoring notebook. The nurses call each patient on the scheduled day, ask about his or her behavior changes and monitor data, then make “step-up goals” for the next month. In addition, based on his or her knowledge and practice level, the nurses provide education using the education booklet. Patients and nurses repeat these activities for 6 months.

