### Outcomes and Data Collection Schedule

Since this is a pilot study, we set various indicators (Multimedia Appendix 5). The primary outcome is set as a change in HbA_1c_. As the secondary outcomes, we set various evaluation indicators. The data collection schedule is also set in Multimedia Appendix 5.

Sociodemographic data, clinical history, and lifestyle are taken at the initial assessment (Initial assessment sheet). Satisfaction is measured by the Likert scale (Satisfaction scale). Achievement of monthly goals is measured by percentage. Behavior change is measured by the researcher-developed scale (Lifestyle behavior questionnaire). Self-efficacy is measured by the Diabetes Management Self-Efficacy Scale.

Qualitative data will be interviewed, described, or recorded when it occurs. Engagement and follow-up rate, education material used, complication management, and “patients who have achieved HbA_1c_ in recommended level” will be counted. Cost-effectiveness will be calculated.

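### The paired pre/post test uses only patients with both HbA1c values, while the protocol expects 30% dropout that is partly disease-related, so the estimate may be biased, probably toward benefit

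*Protocol article*

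**What the plan says.** Protocol article, Outcomes and Data Collection Schedule: "The primary outcome is set as a change in HbA_1c". Design and Period says that after 6 months the team will "compare the baseline (pretest) and the endline (posttest) data of individual participants". Statistical Analysis names the paired t test for normally distributed continuous variables and the Wilcoxon signed-rank test among the options for the others.

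The Sample Size section is built on the same pairing: "we set an effect size of 0.39 considering the differences between 2 dependent matched pair means", "with a level of significance of 5%, and 80% power", and "the total sample size is calculated at 54". It then allows for loss: "we consider a 30% dropout (16 participants) for this study", giving 70. Its reasons for leaving are of two kinds. Consent, withdrawal and migration need have nothing to do with glycaemia. The others do: patients may "change the health care facilities based on the disease severity, complications, hospitalization, etc". The list is open-ended and no proportions are attached.

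On interim data, Process of Providing Education says: "In the third month, patients are requested to visit the PHC for regular follow-up by physician and laboratory test". It does not say which tests are done. Limitations names selection bias from purposive sampling and the absence of a control group, but not attrition.

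**The concern.** A paired test drops every patient without an endline HbA1c. The article does not use the term completers; the restriction follows from the named test. Some of the patients expected to be lost are those whose disease gets worse. The Hypothesis section describes poor management as aggravation, complications and hospitalization, so some patients who fail on the study's own terms are among those expected to have no endline value. Enrolling 70 to keep about 54 pairs protects power. It does nothing about who the remaining pairs are.

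In a controlled trial, similar dropout in the other arm might offset part of such a bias. Here there is one group, so any selection goes straight into the primary estimate. The Principal Findings and Future Perspectives sections tie a significant or effective result to sharing with policymakers and to country-wide scale-up, so a decline seen only in those who stayed could be read as a decline in everyone enrolled.

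**Working it through.** **Inputs from the protocol article.** dz = 0.39, two-sided α = 0.05, power 0.80, 54 pairs, 30% dropout (also given as 16 participants), 70 enrolled. The documents give no HbA1c change for dropouts and no split of reasons. Everything in steps 2 and 3 about dropouts is therefore an assumption.

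**1. The plan's own figure.** Paired t test with df = n − 1 and noncentrality dz·√n. At n = 54: 0.39 × √54 = 2.866, critical t = 2.0057, power = 0.8034. This matches the article's software output. If 30% of 70 leave, 70 × 0.70 = 49 pairs remain, with power 0.763. If 16 leave, 54 remain.

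**2. Completer effect against cohort effect.** In SD-of-change units, with dropout share d, disease-related fraction s of the dropouts, and disease-related leavers changing by m (other leavers behave like completers):

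cohort effect = (1 − d·s) × 0.39 + d·s × m, with d = 0.30.

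| Disease-related fraction s | Leavers unchanged (m = 0) | Leavers worsen (m = −0.39) |
|---|---|---|
| all (s = 1) | 0.70 × 0.39 = 0.273 | 0.70 × 0.39 − 0.30 × 0.39 = 0.156 |
| one third (s = 1/3) | 0.90 × 0.39 = 0.351 | 0.90 × 0.39 − 0.10 × 0.39 = 0.312 |

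The completer result of 0.39 is then 1.43 or 2.5 times the cohort effect in the first row, and 1.11 or 1.25 times in the second. The sign can also reverse. If all leavers improve by 0.60 SD, the cohort effect is 0.70 × 0.39 + 0.30 × 0.60 = 0.453, and completers understate it.

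**3. False-positive rate when there is no true change.** Assume that dropout follows a latent normal variable with correlation ρ to worsening, and that the 30% highest on it leave. The completers' apparent improvement is ρ × φ(z)/0.70 with z = 0.524 and φ(z) = 0.348, which is 0.497ρ SD. The noncentrality at n = 49 is 7 × 0.497ρ.

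| ρ (assumed) | Apparent improvement (SD) | Two-sided rejection, n = 49 |
|---|---|---|
| 0 | 0 | 5.0% |
| 0.1 | 0.050 | 6.3% |
| 0.2 | 0.099 | 10.5% |
| 0.3 | 0.149 | 17.6% |
| 0.5 | 0.248 | 39.9% |

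If loss is 16 of 70 (22.9%) and 54 pairs remain, the rates at ρ = 0.3 and 0.5 fall to 13.6% and 29.3%. These calculations keep the SD of change at 1. Allowing for the smaller variance among completers raises the n = 49 figures at ρ = 0.3 and 0.5 to 18.2% and 44.6%.

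**The case against.** A reader might infer that all of the 30% leave because of worse disease and that the HbA1c improvement will be overstated. The documents support neither. Consent, withdrawal and migration stand in the same list, with no split. No section gives the HbA1c change of dropouts. The section on diabetes in Bangladesh says patients will be helped to seek referral-hospital treatment when needed, so someone who changes facility may reach higher-level care and improve as much as those who stay. This objection stands: the direction is probable, not certain, and the size is unknown.

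It can also be said that analysis sets, missing-data handling and sensitivity analyses are commonly left to a SAP or full protocol, neither of which is shown. Their absence is indeed no finding. But the article does more than stay silent: it names a test that discards patients without an endline value, and it predicts that some will be lost through worse disease. That mismatch is on the page, although an unseen document may already deal with it.

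Two further points stand. The article does not say that HbA1c is part of the month-3 laboratory test, so an interim value cannot be presumed. And a mixed model is valid only if data are missing at random; where dropout follows the unseen month-6 change itself, it removes part of the bias at best.

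Finally, the article already disclaims causal inference and asks for dropout reasons as a feasibility question. The disclaimer concerns the missing control group. It does not cover whether the before/after change describes the patients enrolled.

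**Conclusion.** The point holds as a risk of bias: the primary comparison rests on patients with both values, while the protocol foresees dropout that is partly related to the outcome, and neither the larger sample nor the single-group design corrects for it. The bias is probably toward benefit.

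Under the stated assumptions, a completer effect of 0.39 SD corresponds to a cohort effect of 0.16 to 0.27 SD if all dropout is disease-related and to 0.31 to 0.35 SD if a third is. With no true change, the rejection rate at 49 pairs runs from about 6% to 40% for assumed correlations of 0.1 to 0.5, and stays at 5% if dropout is unrelated to outcome. These ranges illustrate the sensitivity; they do not predict the result. It is a cheap improvement, not a flaw that invalidates the pilot.

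**What to change.** Keep the paired test and add analyses of all 70 enrolled:

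- A sensitivity analysis that sets dropouts' HbA1c change first to zero and then to a stated worsening. It needs no interim data and is the dependable part of the fix.
- A linear mixed model with time as a factor (baseline, month 3 if HbA1c is measured then, month 6), reporting the month-6 minus baseline contrast with a 95% CI and stating that it assumes missing at random.
- A table of dropouts by reason, with baseline and last available HbA1c.

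State in advance that any claim of effectiveness depends on whether the result survives these analyses. According to the Results section, analysis begins only after follow-up is complete, so this can be written down before the data are analysed.

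The cost is a few lines of analysis text, modest extra work in the software already chosen, and a headline effect that may turn out smaller.

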### Statistical Analysis

Descriptive statistics will be expressed as frequencies and percentages for categorical variables and mean with SD or median with quantile, distribution, and range for the continuous variables. To compare the categorical variables between pre- and postdata, the chi-square test will be performed. To compare feasibility and efficacy (pre and post), continuous variables will be compared by paired *t* test or one-way ANOVA for the normally distributed and or McNemar test or Wilcoxon signed-rank sum test for the not normally distributed variables after checking the data normality. Qualitative data will be described and categorized if necessary. Statistical significance will be set as <0.05. Data will be analyzed using IBM SPSS Statistics for Windows, Version 25.0 (IBM Corp).

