## Results

The project was funded in 2024. The enrollment of the participants started on October 26, 2024, and as of February 2025, all the participants (N=70) were enrolled. Data analysis will be started after the completion of follow-up data collection and the first results are expected to be submitted for publication in 2026 if all information is available.

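### The 30% dropout allowance was added to the 54 completers needed instead of dividing by 0.70, so 70 enrolled patients do not give 80% power at 30% dropout

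*Protocol article*

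**What the plan says.** The Sample Size section of the protocol article bases the calculation on the paired change in HbA1c: "we set an effect size of 0.39 considering the differences between 2 dependent matched pair means of HbA_1c_ from a previous study". It continues "with a level of significance of 5%, and 80% power, the total sample size is calculated at 54". The G*Power output in Textbox 1 gives a two-tailed test, noncentrality 2.8659030, critical t 2.0057460, 53 degrees of freedom, n = 54 and actual power 0.8033525.

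The section then lists reasons why patients may leave, including withdrawal, migration, a change of facility and hospitalization. It adds "we consider a 30% dropout (16 participants) for this study" and concludes "Therefore, the total sample size is estimated to be 70".

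The Results part of the abstract reports that "the required sample (n=70) enrollment was completed in February 2025", and the main Results section confirms that "as of February 2025, all the participants (N=70) were enrolled". No other section gives a different dropout rate or defines the allowance in another way.

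**The concern.** A dropout rate describes the patients who enter the study. All the reasons listed in the Sample Size section happen to enrolled patients. To finish with a required number of completers, that number must be divided by the expected retention. The protocol instead multiplied the required completers by the dropout rate and added the product. This always gives too small a total, and the gap widens as the rate rises.

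The percentage and the count in the same sentence therefore cannot both describe the cohort of 70. The primary outcome is change in HbA1c, compared between baseline and endline within each patient, with a paired t test among the listed methods. A patient without an endline value supplies no pair to that test. At the protocol's own dropout assumption, the primary comparison would have less than the stated power, and a null result would be judged against a figure that the design does not reach.

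**Working it through.** **Inputs**, all from the Sample Size section and Textbox 1: dz = 0.39; two-sided α = 0.05; target power 0.80; dropout 30%, stated as 16 participants; 70 enrolled.

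**Step 1. Reproduce the protocol's 54.** For a paired t test with n pairs, the noncentrality is δ = dz × √n and df = n − 1. Power is the probability that a noncentral t variable with these parameters falls outside ± the critical t.

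- n = 54: δ = 0.39 × √54 = 2.8659, critical t = 2.0057, power = 0.8034. This matches Textbox 1.
- n = 53: power = 0.7957, so 54 is the smallest number that reaches 80%.

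The base calculation is correct.

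**Step 2. Reproduce the protocol's 70.**

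- 0.30 × 54 = 16.2, taken as 16; 54 + 16 = 70. Equivalently, 54 × 1.30 = 70.2.

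The protocol's total comes from adding 30% of the completers.

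**Step 3. Apply the rate to those enrolled.**

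- Enrolment needed: 54 / (1 − 0.30) = 77.14, so 78. The shortfall is 78 − 70 = 8 patients.
- Completers from 70 at 30% dropout: 70 × 0.70 = 49, which is 5 fewer than 54.
- Dropout rate that 16 losses represent: 16 / 70 = 22.9%.

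**Step 4. Power with 49 pairs.**

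- δ = 0.39 × √49 = 2.730, critical t = 2.0106, power = 0.763.
- dz detectable with 80% power and 49 pairs: about 0.408.

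**Step 5. Power of 70 enrolled over a range of dropout (dz 0.39).**

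| Dropout from 70 | Pairs | Power |
|---|---|---|
| 0% | 70 | 0.896 |
| 10% | 63 | 0.862 |
| 20% | 56 | 0.818 |
| 22.9% | 54 | 0.803 |
| 30% | 49 | 0.763 |

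**Step 6. Let the number of completers vary.** If each of the 70 patients independently has a 30% chance of dropping out, the probability of keeping at least 54 is about 12%, and the average power is about 0.761. At the stated rate, the planned number of pairs would usually be missed.

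**The case against.** The strongest reply is that the power calculation itself is right. The protocol attaches 80% power to 54 evaluable pairs, which reproduces exactly. It also gives the allowance as a count, and 70 − 16 = 54. On this reading only the percentage is mislabelled. That is a fair account of how the error arose, but it does not remove the contradiction. The 30% is the stated planning rate, and at that rate 70 is too few.

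A second reply is that the power of the running trial is not known to be low. Realised dropout is not in the document, and power stays at or above 80% unless more than 16 of the 70 are lost. This stands. The finding concerns the stated combination of figures, not the power that the trial will turn out to have.

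A third reply is that the loss is small for a single-arm pilot with feasibility aims, and no larger than the uncertainty in the assumed effect: with all 54 pairs, dz 0.37 in place of 0.39 also gives about 0.761. The error biases no estimate and does not raise the type I error. This stands too, and it limits how much weight the point should carry. However, the protocol chose a power-based sample size and a 5% test, and its Discussion makes sharing the results with policymakers depend on significance, so the power it reports should be correct.

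**Conclusion.** The concern holds. The dropout allowance was calculated on the wrong base, and 70 enrolled, 30% dropout and 80% power cannot all be true for dz 0.39. At 30% dropout the study has 49 pairs and 76.3% power, 3.7 points below the 80% target. The stated power is kept for losses of up to 16 of 70 (22.9%). A total consistent with 30% dropout would have been 78.

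These figures assume the protocol's own dz, a two-sided 5% paired t test, and an analysis of patients with both HbA1c measurements. The effect on the trial is modest, but the figure is wrong as written.

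**What to change.** Replace the dropout sentence in the Sample Size section. The new text should say that:

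- 54 evaluable pairs are needed for 80% power at dz 0.39;
- 70 enrolled allows up to 16 losses (22.9% of those enrolled) while keeping those 54 pairs;
- if 30% of those enrolled were lost, 49 pairs would remain, with power of about 76% and a detectable dz of about 0.41 at 80% power.

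The equation of a 30% dropout with 16 participants should go. The results report should use the corrected statement and give the power in terms of the pairs needed, so that readers can set it against the number actually analysed.

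No further recruitment is proposed, since enrolment is complete at 70. The cost is a short rewording and a slightly less favourable power statement; conduct and analysis do not change.
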